### Randomization and Blinding

To ensure the integrity of this study, the following randomization procedures have been implemented. Participants (n=100) are randomly assigned to 1 of 2 groups: the intervention group, “INTeRAcT” (n=50), or the control group, “usual care” (n=50). To achieve a balanced distribution across conditions and prior rehabilitation technology experience, participants are stratified by condition (stroke or SCI) and prior technology experience. The latter refers to previous participation in outpatient rehabilitation involving advanced technological devices at a frequency of at least 1 to 2 sessions per week for a minimum duration of 3 months. Allocation concealment is ensured using preprepared randomization lists with a block size of 2. As participants enter this study, an independent team member responsible for randomization, who is not involved in participant contact or data collection, assigns each participant to the next concealed allocation. Recruiters and assessors have no access to the allocation lists and are unaware of the randomization sequence or block size. To ensure objectivity and minimize bias, outcome assessments are conducted by an assessor blinded to treatment allocation. Group assignment will be revealed to participants after the first measurement (T0). In exceptional cases, early disclosure may occur due to practical arrangements for participation in the 3-week intervention; however, the assessor will remain blinded. Participants are instructed not to disclose their allocation. Physiotherapists, participants after T0, and researchers involved in follow-up, process evaluation, and economic evaluation cannot be blinded.

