### Trial Treatment

#### Experimental Intervention: INTeRAcT Program

The intervention group will receive a total of 90 hours of motor therapy over 3 weeks, 30 hours per week, delivered in 6-hour sessions each weekday. Every 3 weeks, 3 participants will undergo the intervention. The therapy will be provided by trained physiotherapists with expertise in neurological disorders at the clinical site, AZ Herentals (To Walk Again).

This high-dose, intensive-targeted rehabilitation program is evidence-based, grounded in the principles of motor learning, personalized, and goal-oriented. The program aims to enhance physical fitness and independence in daily life through cardiovascular fitness training, therapy for the upper and lower limbs, with and without advanced technological devices, and goal-oriented training. All of this is tailored to the individual participant, considering personal goals and limitations, incorporating built-in progression over time. Additionally, the program emphasizes transferring skills to functional tasks and promoting self-management to improve the participant’s self-efficacy beyond the duration of the program. These components constitute the 7 therapy blocks of the program. All blocks are covered daily in a random order, except cardiovascular fitness training and self-management. Figure 3 illustrates an example of a weekly schedule that outlines the various therapy components.

During the baseline (T0) assessment, 3 specific goals will be defined by the participant, in collaboration with a KU Leuven researcher with a master’s degree in neurological physiotherapy, using the Goal Attainment Scaling (GAS) [97,98], which will serve as the focus throughout the 3-week intervention. Based on these goals, the physiotherapist will evaluate which subgoals are still needed to achieve the goal. The overall structure of the program follows a four-step process: (1) setting personalized goals; (2) evaluating and observing the activity to identify the subgoals contributing to the main problem; (3) practicing these subgoals to address underlying difficulties during components 1‐5, as outlined below; and (4) practicing the full activity during the goal-oriented therapy sessions (component 6), as outlined below.

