During the 3-week intervention period, the intensive therapy is documented daily in diaries by the physiotherapists, including the total number of minutes of therapy, the division between active therapy time (eg, performing active repetitive movements) and other therapy time (eg, explanation, resting periods, and ADL tasks), and the content of each of the 7 therapy blocks. Additionally, at the end of each therapy block, the Borg Rating of Perceived Exertion Scale [105] is completed to assess participants’ subjective experiences of physical exertion. This scale ranges from 6 (“no exertion at all”) to 20 (“maximal exertion”) and allows for individualized adjustments to training intensity. Outside the 6-hour daily intervention sessions, participants were permitted to continue their usual care, which was recorded in diaries. The intervention was described according to the TIDieR (Template for Intervention Description and Replication) checklist, provided in Checklist 1.

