#### Control Intervention: Usual Care

To allow a pragmatic comparison with current clinical practice, the control group will continue their usual care at home or in an outpatient rehabilitation center or hospital for the entire 9-month study period, without receiving any alternative interventions. After completing this study, participants in the control group will be given the opportunity to receive the identical 3-week program following the final follow-up measurement at 9 months. This waitlist-control design will help maintain participants’ motivation to adhere to this study during the 9-month follow-up period.

Participants will document their usual care in therapy diaries (Figure 1), with assistance from their therapist if needed. These diaries will capture the frequency (number of sessions), intensity, and time (duration), and type (therapy content) of physiotherapy, occupational therapy, and psychological sessions, in line with the FITT (Frequency, Intensity, Time, and Type) principles [101]. The diaries were developed by the research team based on expert input, and their content was reviewed and approved by clinicians. Participants in the intervention group will complete the same diaries during the follow-up period, after the 3-week intervention. The diaries will be collected and reviewed monthly, and any missing data will be requested from participants.

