#### Data Analysis

First, a trial-based health economic evaluation will be conducted to assess the cost-effectiveness of the intensive, personalized rehabilitation program compared to usual care. Individual participant data from both the intervention and control group will be used to estimate the costs and health effects of the intensive personalized rehabilitation program compared to usual care from baseline up to 9 months of follow-up. The cost-effectiveness of the intervention will be expressed in incremental cost per QALY gained, calculated as the incremental cost-effectiveness ratio (ICER):

$$ICER=\frac{\left({\text{mean expected cost}}_{\text{intervention}}-{\text{mean expected cost}}_{\text{control}}\right)}{\left({\text{mean expected effect}}_{\text{intervention}}-{\text{mean expected effect}}_{\text{control}}\right)}=\frac{€}{\text{QALY}}$$

The robustness of the results will be evaluated through a deterministic and probabilistic sensitivity analysis of both costs and effects. A univariate deterministic sensitivity analysis will be conducted to assess the relative impact of individual cost components on the ICER. The results will be visually presented using tornado diagrams. A probabilistic sensitivity analysis will be performed using bootstrapping with replacement, with a minimum of 1000 iterations, to estimate the 2.5% and 97.5% percentiles of the ICER distribution. As all costs occur within a 1-year timeframe, no discounting will be applied. All bootstrapped ICERs will be visualized on a cost-effectiveness plane to assess the uncertainty surrounding the ICER and the probability that the intervention is cost-effective at various willingness-to-pay thresholds. To illustrate these probabilities of acceptable ICERs, a cost-effectiveness acceptability curve will be used. In addition, exploratory subgroup analyses will be considered based on pathology, type and severity of stroke and SCI, and total rehabilitation dose.

Given the extensive data collection in this trial, some missing data may occur; therefore, appropriate data imputation techniques will be applied [136]. The analysis will be conducted using R (R Foundation) software, following the Belgian guidelines for health economic evaluations [137], and will be reported according to the Consolidated Health Economic Evaluation Reporting Standards [138].

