Second, we will perform a model-based health economic evaluation. Conventional practice guidelines for cost-effectiveness analysis recommend using a time horizon that is sufficiently long to capture all relevant costs and outcomes, particularly for interventions targeting chronic conditions. In this case, a lifetime horizon as the base case analysis is often suggested [139,140]. As the absence of long-term follow-up data should not justify the failure to extend the time horizon to a relevant duration [140], a Markov model will be developed. This approach will allow us to account for the expected costs and health outcomes in both intervention and control groups beyond the follow-up period, to estimate the cost-effectiveness over a lifetime horizon. Estimates of resource use and utilities for each health state are derived from international peer-reviewed literature. Special attention will be given to the transferability of this data to the Flemish health care context, validated through monitoring within the research consortium. Discount rates of 3% for costs and 1.5% for utilities will be applied, following the Belgian guidelines [137]. In line with the trial-based evaluation, probabilistic sensitivity analyses will be conducted to account for uncertainty around the input parameters. R software to develop the model, calculate the incremental cost per QALY, and perform the probability sensitivity analysis.

Lastly, several scenario analyses will be conducted to simulate various implementation models of the intensive program compared to current usual care, such as providing 1‐2 intensive rehabilitation boosts per year, rather than dispersing the same therapy volume across an entire year (eg, 1‐2 h of therapy each week for a year).

A budget-impact analysis will also be performed to assess how the introduction of this intensive therapy might affect the care budgets. This analysis will consider (1) the annual incidence of the specific population for whom this therapy is suitable, (2) the number of centers required to provide this therapy, (3) the planning timescale, and (4) the total cost of expanding this therapy across Flanders.

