Second, this study includes 2 patient populations, resulting in a heterogeneous sample. However, both populations share the common characteristic of having an acquired neurological condition in adulthood, typically presenting with similar primary symptoms such as paresis, motor and sensory impairments, and secondary complications including spasticity and cardiovascular issues. Together, these symptoms significantly affect patients’ mobility and functional independence, leading to comparable rehabilitation needs. Moreover, the recovery trajectories in both groups are comparable, with a critical window for motor recovery typically occurring in the first months after onset [14,15,18]. Nevertheless, evidence indicates that motor improvements remain achievable in the chronic phase, driven by exercise-dependent plasticity [19,23,24,34]. The INTeRAcT program also incorporates principles of motor learning, which are relevant and applicable to both patient populations [14,146]. This broader inclusion enhances the generalizability of the findings to other neurological conditions, thereby increasing the relevance and applicability of the results beyond the specific populations studied. Therefore, evaluating both populations within a single trial can be considered appropriate.

Third, as this study is designed as a pragmatic trial, the control group receives usual care, reflecting the current real-life clinical context. The inherent variability in usual care may influence clinical outcomes; therefore, both the total amount of therapy and the content delivered are documented, as outlined in the Methods section.

Lastly, although the goal-directed nature of the program provides a clear source of motivation for patients [147,148], the self-enrollment procedure may attract more motivated individuals, potentially introducing selection bias. However, this phenomenon likely reflects clinical reality, where patients with higher intrinsic motivation are more inclined to participate in continued care. The process evaluation will provide crucial insights into the extent to which patient motivation contributes to the observed outcomes.

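### Total rehabilitation dose is named as a subgroup factor for the between-arm ICER, but it accrues after randomisation and contains the allocated 90 hours, so arms compared within dose strata are not a randomised comparison

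*Protocol article*

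**What the plan says.** The Data Analysis section of the Health Economic Evaluation defines the ICER as the intervention-minus-control difference in mean cost over the same difference in mean effect. It then adds that "exploratory subgroup analyses will be considered based on pathology, type and severity of stroke and SCI, and total rehabilitation dose".

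Other sections show what total dose is made of:

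- Experimental Intervention: "The intervention group will receive a total of 90 hours of motor therapy over 3 weeks". Outside the daily sessions, "participants were permitted to continue their usual care, which was recorded in diaries".
- Control Intervention: "the control group will continue their usual care at home or in an outpatient rehabilitation center or hospital for the entire 9-month study period".
- Discussion, on variability of usual care: "both the total amount of therapy and the content delivered are documented". Dose is therefore observed during the trial and is not a baseline characteristic.
- Randomization and Blinding: "participants are stratified by condition (stroke or SCI) and prior technology experience". Dose is not a stratification factor, and could not be one.

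The protocol does not define dose as therapy received before randomisation, does not confine the dose analysis to one arm, and does not label it non-randomised. In the clinical Data Analysis section, subgroups are by pathology only, and therapy received is reported descriptively.

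**The concern.** A subgroup comparison keeps the protection of randomisation when the subgroup is fixed before allocation. Total dose is not, and it contains the treatment itself. For a control to reach the same total as an intervention participant, that control must use about 90 more hours of usual care. Grouping by total dose therefore matches people on a sum while making them differ on usual care, the part that was not allocated.

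Therapy hours are also a component of the costs in the ICER numerator, so the imbalance enters incremental cost directly. If usual-care use is related to prognosis, it enters incremental QALYs as well. An ICER that differs between dose strata could then look like evidence about dose when no real effect modification exists. The stated purpose of the economic evaluation is to support reimbursement decisions, so such a table should not be open to that reading.

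**Working it through.** The plan prints no figure on this point to reproduce, so the check is structural, with illustrative numbers.

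**Inputs from the protocol.** 90 h allocated to the intervention arm; 50 participants per arm; 9 months of follow-up (about 39 weeks).

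**Inputs assumed.** Usual-care hours over 9 months, because none are stated. The only weekly therapy figure is the 1-2 "h of therapy each week for a year" in an implementation scenario, which is not a statement of usual care. Over 39 weeks it would be 39 × 1 = 39 h to 39 × 2 = 78 h.

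**Step 1: how far allocation fixes dose.** Let D = U + 90A, with U the usual-care hours (same distribution in both arms) and A = 1 for intervention. With equal arms, Var(90A) = 90² × 0.25 = 2025, so the share of dose variance explained by arm is 2025 / (2025 + SD²).

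- SD 40 h: 2025 / 3625 = 56%
- SD 60 h: 2025 / 5625 = 36%
- SD 80 h: 2025 / 8425 = 24%
- SD 120 h: 2025 / 16425 = 12%

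**Step 2: who lands in each half.** Simulation with U gamma distributed, full delivery of the 90 h and a split at the pooled median of D. For mean 100 h and SD 60 h:

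| Half by total dose | Share intervention | Usual care, intervention | Usual care, control | Difference |
|---|---|---|---|---|
| Low | 21% | about 34 h | about 75 h | about -41 h |
| High | 79% | about 117 h | about 192 h | about -75 h |

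With 50 per arm, each minority cell holds about 50 × 0.21 = 10 to 11 people. For means of 60-150 h and SDs of 40-80 h the upper half is 72% to 89% intervention. With SD 120 h and means of 150-200 h it is about 66%.

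**Step 3: effect on incremental cost.** Let r be the cost of one usual-care hour and P the programme cost per participant. If allocation does not change usual care, the randomised contrast in therapy cost is P. Within strata, in the scenario above, it becomes P - 41r (low) and P - 75r (high). The shift comes from the grouping alone and needs no link between usual care and prognosis.

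**Step 4: effect on incremental QALYs.** A second simulation used weekly usual care with means of 1-5 h (SD 0.5-4 h) over 39 weeks, 85-100% delivery of the programme, a true effect of 0.03 QALY in everyone and a QALY SD of 0.15. Within-stratum usual care was 29-38 h lower for intervention participants in the low half and 64-83 h lower in the high half.

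| Correlation of usual care with worse prognosis (assumed) | Apparent effect, low half | Apparent effect, high half |
|---|---|---|
| 0 | about 0.03 | about 0.03 |
| 0.3 | 0.04 to 0.10 | 0.05 to 0.18 |
| 0.5 | 0.05 to 0.14 | 0.07 to 0.28 |

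The bias changes sign with the correlation. At mean 2 h/week and SD 1, a correlation of 0.3 gives 0.075 in the low half, a bias of 0.075 - 0.03 = +0.045. If heavier users had the better prognosis to the same degree, the result would be 0.03 - 0.045 = -0.015.

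**The case against.** The best case for leaving the text alone has four parts.

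- **Status.** The analysis is exploratory and only to be considered. It does not touch the primary outcome, the clinical model, the base-case ICER or its bootstrap. This stands and limits the weight of the point. It does not remove it, because an exploratory label deals with multiplicity and not with selection.
- **Implementation left open.** The protocol defines neither dose nor a cut-point, and does not say that the arms are pooled for the split. A usual-care-only dose or a declared dose-response description remains possible. This stands in part: the flaw arises if arms are compared within total-dose strata. That is nonetheless the natural reading, because dose is listed beside ordinary subgroup factors for a between-arm ratio.
- **Hours unknown.** A reader might infer that the 90 hours largely determine total dose. That holds when usual care is low or uniform, but the Discussion stresses its variability, and at SD 120 h arm explains only 12% of dose variance. The document cannot settle this.
- **Prognosis unknown.** A reader might also infer that high-dose controls are sicker, so that the subgroup ICERs are certain to be confounded on effect. Nothing in the document links heavier usual care to worse prognosis. Heavier users could equally be more motivated, and with no such link the QALY difference is unbiased.

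The usual-care imbalance survives all four: it appeared in both halves in every scenario tabulated, and it reaches incremental cost without any assumption about prognosis.

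**Conclusion.** The point holds as a minor one. Total rehabilitation dose is a post-randomisation quantity that includes the allocated treatment and is part of cost, and no other section repairs its use as a subgroup factor. If arms are compared within total-dose strata, the comparison is not randomised and incremental cost is distorted. Incremental QALYs are biased only to the extent that usual-care use is related to prognosis, and the direction is not established.

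The size rests on assumed usual-care hours and a median split: an upper half about 66% to 89% intervention, and, at mean 100 h and SD 60 h, usual-care gaps of about 41 h and 75 h. The documents do not support saying that the main cost-effectiveness result is affected, that dose is mostly fixed by allocation, or that the high-dose controls are the sicker ones.

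**What to change.** Remove total rehabilitation dose from the subgroup factors for the between-arm ICER. Restrict those factors to characteristics fixed before randomisation: pathology, type, severity stated as baseline severity, and, if wanted, the prior technology-experience stratum. That stratum answers a different question from dose and is optional. Test each factor as a treatment-by-factor interaction on net benefit.

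Report delivered dose descriptively, as the clinical Data Analysis section already plans. If a dose analysis is still wanted for the economic paper, define dose and label the result as a non-randomised dose-response description.

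The cost is a few words in the text and one exploratory table lost or relabelled. No new data are needed. Data analysis is described as ongoing, so the change should be made and dated before any dose-stratified ICER is produced.

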## Introduction

Worldwide, 1 in 4 people over the age of 25 years will experience a stroke in their lifetime, resulting in nearly 12 million new strokes each year [1]. In 2021, there were 1.74 million incident stroke cases and 13.4 million prevalent stroke cases reported in Europe [1]. Predictions indicate that by 2030, an additional 3.5% of the adult population will have experienced a stroke [2]. For spinal cord injury (SCI), the incidence in Europe was estimated at 108,000 new cases in 2019, with 2.67 million individuals living with SCI [3].

Both conditions contribute to a significant disease burden [1,4], affect multiple domains of human functioning [5], and are associated with a reduced quality of life [6,7]. Motor problems are the most common impairment [8,9], affecting 60%‐75% of patients after stroke [9] and even more than 80% of individuals with SCI [10], even in the chronic phase [10,11]. Thus, despite completing standard rehabilitation in the subacute phase, deficits remain present in a large number of patients. Motor impairments can involve both the upper and lower limbs, leading to significant limitations in locomotion [12,13] and dependency during daily functioning [11]. To date, there is no cure for poststroke and post-SCI deficits, but rehabilitation can effectively address motor impairments such as reduced strength and balance, as well as functional limitations in performing activities of daily living (ADLs).

In the literature, the so-called “critical window” describes a period of heightened neuroplasticity during which the greatest motor recovery occurs, typically within the first 3 months following a stroke or SCI [14-18]. Around 6 months postonset, motor recovery tends to plateau and generally remains below prepathology function [14-18]. However, Ballester et al [19] demonstrated that an increased sensitivity to rehabilitation can persist beyond 1 year after stroke. A similar phenomenon has been observed in chronic SCI, where several studies have reported motor improvements more than 1 year after onset [20-22]. These findings suggest that patients retain the capacity to enhance their functional abilities through exercise-dependent plasticity [23,24]. Despite this ongoing potential for improvement in the chronic phase, rehabilitation services during this phase remain limited within the current health care system.

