### Participant Selection and Recruitment

In this randomized controlled trial, adults in the chronic phase after a stroke or SCI, living in Belgium, participated. Recruitment was conducted via databases (Stroke Rehabilitation Research Team, KU Leuven/To Walk Again), information sessions in hospitals and rehabilitation centers, and outreach to participant associations and adaptive sports centers in Belgium. First-line health care providers, including general practitioners, physiotherapists, speech therapists, home care nurses, and pharmacies, were encouraged to inform potential participants.

The inclusion criteria were (1) first stroke or SCI (American Spinal Injury Association Impairment Scale: A, B, C or D; (A) complete: no sensory or motor function is preserved in sacral segments S4-S5; (B) incomplete: sensory, but not motor, function is preserved below the neurologic level and extends through sacral segments S4-S5; (C) incomplete: motor function is preserved below the neurologic level, and most key muscles below the neurologic level have a muscle grade of less than 3; and (D) incomplete: motor function is preserved below the neurologic level, and most key muscles below the neurologic level have a muscle grade that is greater than or equal to 3) with a clear participant need related to the upper and/or lower extremities, diagnosed by a medical specialist more than three months ago; (2) living at home and more than three months postdischarge from a hospital or rehabilitation center; (3) a maximum recovery of 85% independence in daily functioning, assessed using the Functional Independence Measure (FIM) for stroke or the Spinal Cord Independence Measure (SCIM) for SCI; (4) a prepathology Barthel Index >85/100; (5) unilateral or bilateral weakness of the affected upper and/or lower limbs, with no maximum score of five on all three segments of the Motricity Index; (6) age ≥18 years; and (7) clinical and cognitive ability to perform high-dose rehabilitation with advanced technology, as assessed by a medical doctor (MD).

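### The budget-impact analysis counts only new cases per year, although the programme is for people already living with chronic stroke or SCI; early-year demand is likely to be understated

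*Protocol article*

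**What the plan says.** The last paragraph of the model-based evaluation (Protocol article, Health Economic Evaluation, Data Analysis) names four things the budget-impact analysis will consider. The first is "the annual incidence of the specific population for whom this therapy is suitable". The second is the number of centers needed. The rest are "the planning timescale, and (4) the total cost of expanding this therapy across Flanders". Prevalence is not mentioned there.

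The target population is described under Participant Selection and Recruitment: "adults in the chronic phase after a stroke or SCI, living in Belgium, participated". Stroke or SCI must have been "diagnosed by a medical specialist more than three months ago", and discharge must also lie more than three months back. Neither condition has an upper time limit. A functional ceiling applies: "a maximum recovery of 85% independence in daily functioning".

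The Introduction reports new and existing cases separately. For stroke it gives "1.74 million incident stroke cases and 13.4 million prevalent stroke cases reported in Europe" in 2021. For SCI, "the incidence in Europe was estimated at 108,000 new cases in 2019, with 2.67 million individuals living with SCI".

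**The concern.** Incidence measures a yearly inflow. A programme open to anyone in the chronic phase, however long after onset, can be claimed on the day of introduction by everyone already living with the condition who meets the criteria. That stock is absent from an incidence count. The Introduction distinguishes incident from prevalent cases for both conditions, so the choice of term in the budget-impact list is hard to read as loose wording.

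The aim of the economic work is to inform reimbursement, and the Discussion names the federal health and disability insurer as a key stakeholder. The center count (second input) and the total cost across Flanders (fourth input) both depend on the population count. If that count leaves out the existing stock, the payer sees too small a demand in the first years, and the error makes the programme look more affordable.

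**Working it through.** The article states no budget-impact result (no eligible number, cost or horizon), so there is no figure to reproduce. The check asks how far an incidence-only count could fall short, using the article's own counts.

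**Inputs** (Introduction, Europe, in millions)
- Stroke: I = 1.74 incident, P = 13.4 prevalent.
- SCI: I = 0.108 incident, P = 2.67 prevalent.
- Combined: I = 1.74 + 0.108 = 1.848; P = 13.4 + 2.67 = 16.07. The stroke counts are for 2021; the SCI incidence is for 2019.

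**One-year pool, equal eligible share among prevalent and incident cases (assumption): P / I**
- Stroke: 13.4 / 1.74 = 7.7
- SCI: 2.67 / 0.108 = 24.7
- Combined: 16.07 / 1.848 = 8.7

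**One-off treatment over T years.** Let r be the eligible share among prevalent cases relative to incident cases (assumed; the article gives none). Each patient is treated once, and the first year's new cases are counted inside the prevalent stock:

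ratio = (r × P + I × (T − 1)) / (I × T)

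Example, combined, r = 1, T = 3: (16.07 + 1.848 × 2) / (1.848 × 3) = 19.766 / 5.544 = 3.6.

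Example, combined, r = 0.25, T = 5: (4.0175 + 1.848 × 4) / (1.848 × 5) = 11.4095 / 9.24 = 1.2.

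| Combined ratio | 1 year | 3 years | 5 years | 10 years |
|---|---|---|---|---|
| r = 1 | 8.7 | 3.6 | 2.5 | 1.8 |
| r = 0.5 | 4.3 | 2.1 | 1.7 | not computed |
| r = 0.25 | 2.2 | 1.4 | 1.2 | not computed |

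By condition at r = 1, stroke alone gives 3.2, 2.3 and 1.7 over 3, 5 and 10 years; SCI alone gives 8.9, 5.7 and 3.4.

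**Limits of the formula.** It ignores deaths and assumes that all eligible people are treated. Its one-year value drops below 1 if r is under 1.848 / 16.07 = 0.115, because the stock is then made to absorb the first year's inflow. If the stock is instead added on top of a full T years of inflow, the ratio is 1 + r × P / (I × T), which exceeds 1 for any positive r. The direction of the omission therefore does not depend on r; its size does.

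**Centers.** Under Experimental Intervention, the trial site treats 3 participants every 3 weeks, which is 52 / 3 × 3 = 52 a year if run continuously. At a fixed throughput, the centers needed to meet demand scale in proportion to the population count.

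**The case against.** The strongest reply is that one sentence in a condensed article is being treated as a whole model. The analysis will consider four items; no formula, base-case population, uptake or horizon is given, and the timescale and center count are where phase-in and capacity would enter. This is fair as to missing detail, which may sit in a fuller plan. It does not rescue the item that is stated: the only population measure named does not match the population the programme is for.

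A reader might infer that the eligible number and total cost will certainly be understated about 8-fold for stroke and 25-fold for SCI. The documents do not support that. The counts are European, while the analysis concerns Flanders. They are not filtered for first event, living at home, the independence ceiling or fitness for high-dose therapy, and nothing shows that the eligible share is equal in the two groups. The ratios also shrink as the horizon lengthens. If capacity binds, early spending follows the number of centers rather than the size of the pool. Incidence of newly suitable patients is also the right yearly inflow for one-off treatment once the backlog has cleared.

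A reader might also infer that the scenarios with 1–2 boosts per year prove that incidence cannot work. Those scenarios belong to a separate analysis of implementation models and are not stated as budget-impact inputs, and repeat courses can be costed within an incident cohort. They are a reason to state the repeat-use assumption, no more.

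Finally, the point is remote from the main results. Data Handling and Dissemination places the budget-impact analysis in a later publication, so the input can still be corrected without touching trial data.

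**Conclusion.** The point holds as a mismatch with a known direction and an uncertain size. An incidence-only population omits the existing eligible stock and is likely to understate early-year demand, the centers required and the budget.

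The 7.7 (stroke) and 24.7 (SCI) ratios are one-year illustrations, resting on unfiltered European counts and an assumed equal eligible share. For one-off treatment over 3 to 10 years at equal share, the combined shortfall is about 3.6-fold down to 1.8-fold. With prevalent cases a quarter as likely to be eligible, it is about 1.2-fold over 5 years. These are ratios of eligible people, not of spending, which also depends on uptake and center capacity.

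The primary clinical analysis, the trial-based cost-utility analysis and the lifetime cost-effectiveness estimate are unaffected.

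**What to change.** Replace the first budget-impact input with the number of prevalent eligible cases in Flanders at introduction, plus annual incident cases reaching the chronic phase, minus deaths, reported separately for stroke and SCI. State the assumptions on uptake, repeat use and center capacity for each year of the planning timescale. Derive the number of centers from the same counts. Keep the incidence-only count as a labelled steady-state scenario, since it describes one-off treatment after the backlog has cleared.

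The cost is small: one additional epidemiological input per condition (prevalence), the stated assumptions, and a sentence or two of text. No participant data are needed, and the change can be made before the budget-impact paper is written. The likely consequence is a less favourable budget figure for the first years.
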